#### Procedure, sample, and data collection

*Training for professionals at the clinics* will integrate the communication competences and will be designed based on the HAPA model. A *short manual* will be provided to support the participants in implementing the lessons they learn into their working practice. Written documentation of the training will also be provided to avoid failure of implementation. The training will be offered to all professionals at both intervention sites. Its effectiveness will be tested in the pre-experimental study, which aims to investigate the association between training participation and the reduction/occurrence of pAEs, to observe the mechanisms that make the training successful with regard to supporting professionals in their work and understanding how patient training can be implemented in Phase 2.

The study (Stage E of Phase 1) has a one-group, pre−/post-design (see Fig. 4 in Appendix). It includes all professionals (e.g., doctors, nursing staff, midwives/obstetricians, training assistants, psychologists) at all locations and intends to recruit a total of *N* = 140 participants without any participant exclusion criteria. Professionals will be trained in interdisciplinary groups of 10 to 12 participants. Recruitment will take place via the hospitals involving line managers, works councils, quality management departments, and HR departments. They will be involved to ensure adequate participant enrollment to reach target sample size. Participants will be included in the analysis only if they provide informed consent, which will be collected by project managers working at the hospitals. Data will be analyzed according to intention to treat. If study participants withdraw their consent to be contacted for follow-up measurements at any point, their contact details will be removed from the database. If they indicate that they do not want their data included in the analyses, their data will also be removed. Otherwise, they will be considered as study dropout. All target criteria are shown in Table 2.

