#### Statistical analyses

Training effects will be tested by evaluating differences between the measurement times using linear and general mixed models. Baseline values of the first measurement time point will be considered as covariates. Clinics are modeled as fixed effect. Key demographic variables such as age, gender and occupation will be used to calculate selectivity in dropout rates. Missing data per measurement point, but also over time, will be treated by advanced methods to handle missing data such as the full information maximum likelihood method (FIML; this will be the same in all other phases, too).

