### Phase 2: quasi-experimental efficacy study

#### Aim/overview of research questions and methods

In Phase 2 (see Fig. 2 and Fig. 5 in Appendix), the effectiveness of the communication competences intervention for the target group of patients and their social support providers will be tested using the gold standard, i.e. a randomized control trial (RCT). This intervention will be based on all stages of Phase 1 of this project, and thus will be developed in a participatory approach with patients and professionals working in the clinics [63]. The intervention will enable patients and social support providers to gain knowledge about the prevalence of pAEs and communication problems as well as expectations of action results. Moreover, it will allow participants to practice communication competences and develop their self-efficacy. Furthermore, the intervention will utilize the provided theoretical input in order to integrate theory into everyday hospital life by means of action and coping plans. To implement the acquired competences as effectively as possible, the following three components will be addressed in the intervention [65]:
the motivation or intention to communicate effectively and confidently with each other,the knowledge of what is crucial for effective communication,the ability to communicate effectively.

The intervention is based on the HAPA model as a social-cognitive model for behavioral change [25] and communication competences (see description of the training above in Phase 1). Participants will be trained in groups by specialized instructors over the course of one and a half days in facilities of the participating clinics (see Table 5, and  Fig. 5 in Appendix).

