#### Procedure

In each hospital, four *professionals will be taught in a train-the-trainer seminar* to train patients and their social support providers based on the short manual developed to teach communication competences. Recruitment will take place via the doctors, nurses and midwives in the hospitals (Fig. 5 in Appendix). The quality management departments will be involved to ensure adequate enrollment in order to reach the target sample size of N = 423 participants. Informed consent will be collected by on-site project managers. When an expectant mother is admitted to the clinic and agrees to participate in the study, she will be randomly assigned to a training group (IG) or a control group (CG). If she is accompanied by a partner, relative, or close friend, they will be assigned to the same group. All patients and social support providers randomly assigned to the intervention group will receive the same training content over the course of this study. In contrast, the control group will receive the hospital care-as-usual (see Fig. 5 in Appendix).

*Randomization* will be done per site and day (block randomization). The central project coordinator will generate the allocation sequence. Depending on this sequence, all patients admitted to the hospital on that day will be allocated to either the IG or to the CG. Patients and staff will not be informed beforehand on which days allocation to the IG or the CG takes place to prevent biases. Instead, the on-site project manager at each hospital will receive a sealed envelope each day containing this information, enabling them to inform other staff involved as well as enroll and assign participants to the CG or IG treatment. This process allows trial participants, general care providers, outcome assessors and data analysts to remain blinded throughout the allocation sequence. Trial participants and general care providers will be unblinded in case they ask for more information about the training. Revealing a participant’s allocated intervention during the trial can be performed after completion of the IG treatment to disclose the content of the intervention. A flyer will be provided containing this information, which will be also used after the study to disseminate findings and tools. Inclusion and exclusion criteria are outlined in Table 6.

**Table 6 Tab6:** Summary of the inclusion and exclusion criteria

*Inclusion criteria*	*Exclusion criteria*

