Expectant mother or *patient* in gynecology and obstetrics or *social support providers* (spouse/partner, relative, close friend) to be recipient of the training *Professional* in a gynecology and obstetrics hospital to be trainer of the patients and the social support providers	Not proficient in the German language and/or does not have the capability of writing Severe cognitive deficits (unable to read/write/answer questions) and impairments due to diagnosed brain injuries, neurological disorders, etc. Insufficient corrected eyesight (patients must be able to read on the cell phone) Participation in another research study or intervention trial conducted in the clinic
Aged 18 years and above	Younger than 18 years
Healthy volunteers	High risk, emergency case
Declaration of consent for participation in the study	Withdraw of consent for participation in the study at any point in time

According to a power analysis, a sample of *N* = 352 is necessary (alpha error = 0.05, power = 80%, to be analyzed IG _analysis_: *N* = 176; CG _analysis_: *N* = 176) in order to detect an effect size of *d* = 0.3. With an assumed drop-out rate of 20%, *N* = 423 participants (IG _recruited_: *N* = 212; CG _recruited_: *N* = 211) have to be recruited in the study. The pAEs will be collected on an individual basis (anonymized) and coded according to the communication competences (see Fig. 5 in Appendix).

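### Training is delivered in groups, but no training-group term is named in the analysis and the Phase 2 sample size makes no allowance for clustering

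*Protocol article*

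**What the plan says.** **Phase 1.** The study is a one-group pre/post design that "intends to recruit a total of *N* = 140 participants without any participant exclusion criteria" (Procedure, sample, and data collection). The same section states: "Professionals will be trained in interdisciplinary groups of 10 to 12 participants". The Phase 1 Statistical analyses section says: "Training effects will be tested by evaluating differences between the measurement times using linear and general mixed models". Baseline values are covariates, and "Clinics are modeled as fixed effect". The random effects of the mixed models are not listed.

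**Phase 2.** "Participants will be trained in groups by specialized instructors over the course of one and a half days" (Aim/overview of research questions and methods). Group size is not given. Controls receive care as usual, so only one arm is grouped by training. Randomisation is by site and day: "all patients admitted to the hospital on that day will be allocated to either the IG or to the CG" (Procedure). The power statement in the same section says that "a sample of *N* = 352 is necessary", with 176 per arm, alpha 0.05, power 80% and d = 0.3. The Phase 2 analysis follows Phase 1 in using linear and general mixed models, and it adds a dyadic analysis of mothers and their social support providers.

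**Phase 3.** App users will already have completed the face-to-face training. Group differences are again tested with mixed models, and 176 is again the number to be analysed in the new intervention group.

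**The concern.** People trained in one session share a trainer, a date and a set of discussions. The planned training content (Tables 4 and 5) is built on interaction: case discussion, shared reflection and feedback, and networking breaks. Responses to training may therefore be correlated within a session. Clinic, the only grouping factor named, has two levels and does not capture variation between sessions inside a clinic.

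Two things are at stake. The first is the standard error: if session variance exists and no term represents it, intervals are too narrow and false positives too frequent. The second is the stated power: whatever model is fitted later, a sample size calculated for independent observations does not deliver 80% power when one arm is clustered and nothing else compensates.

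**Working it through.** **Inputs from the protocol article.** Phase 1: N = 140, groups of 10 to 12, hence 140/12 = 11.7 to 140/10 = 14, or about 12 to 14 sessions. Phase 2: 176 per arm analysed, d = 0.3, alpha 0.05, power 80%; the trained arm is grouped and the control arm is not.

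**Assumed inputs.** The ICC is not in the documents; 0.02, 0.05 and 0.10 are used. Group size m = 11 lies within the staff range. For Phase 2 patients it is an assumption carried over from staff. Total outcome variance is taken as equal in the two arms.

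**1. Reproducing the plan's figure.** A two-sided two-sample t-test with independent observations, d = 0.3, alpha 0.05 and power 80% needs 175.4 per arm, rounded up to 176, or 352 in total. This matches exactly. A one-sided test gives 138 per arm and does not match. The stated N therefore corresponds to a design effect of 1.

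**2. Phase 1 (pre/post change).** Here the ICC is that of the change score.
- Design effect: DE = 1 + (m − 1) × ICC = 1 + 10 × ICC
- True SE / naive SE = √DE
- Type I error if clustering is ignored = 2 × [1 − Φ(1.96/√DE)]

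| ICC of change | DE | SE ratio | Effective n of 140 | Type I error |
|---|---|---|---|---|
| 0.02 | 1.2 | 1.10 | 117 | 7.4% |
| 0.05 | 1.5 | 1.22 | 93 | 11.0% |
| 0.10 | 2.0 | 1.41 | 70 | 16.6% |

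A simulation with 12 groups of 12 shows when this applies. A stable group difference, present before and after training, cancels in the change score (false-positive rate 4.8%). A session-specific training effect does not cancel: the rate is 6.2%, 11.5% and 17.0% at change-score ICCs of about 0.01, 0.05 and 0.09.

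**3. Phase 2 (trained arm only).**
- Variance inflation of the arm difference: VIF = (DE + 1)/2
- Power = Φ(0.3/√(2/176 × VIF) − 1.96)
- Type I error if clustering is ignored = 2 × [1 − Φ(1.96/√VIF)]

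| ICC | VIF | 0.3/SE | Power | Type I error if ignored |
|---|---|---|---|---|
| 0 | 1.00 | 2.81 | 80% | 5.0% |
| 0.02 | 1.10 | 2.68 | 77% | 6.2% |
| 0.05 | 1.25 | 2.52 | 71% | 8.0% |
| 0.10 | 1.50 | 2.30 | 63% | 11.0% |

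**4. Sensitivity to the assumptions.**
- Groups of 4 at ICC 0.05: DE = 1.15, VIF = 1.075, power about 77%.
- Baseline adjustment with an assumed T1–T2 correlation of 0.5 multiplies the variance by 1 − 0.5² = 0.75. With groups of 11 at ICC 0.05, 0.75 × 1.25 = 0.94, and power is about 83%. At ICC 0.10, 0.75 × 1.50 = 1.125, and power is about 76%. With the same adjustment and no clustering it would be about 90%.

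**The case against.** A reader might infer that the model contains nothing but a clinic fixed effect and that training groups are ignored. The text does not support this. It specifies mixed models, which contain random effects, without listing them, and it plans a dyadic analysis. The list of random effects and the method for degrees of freedom are ordinary content of a full protocol or SAP, so all that can be said is that training group is not named. It is equally tempting to say that standard errors are too small throughout Phases 1 to 3. That is conditional:

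- In Phase 1 it needs session-specific training effects, on which the documents give no evidence.
- In Phase 3 the link is indirect, through earlier face-to-face training whose grouping is not described; no size is claimed there.
- In Phase 2 the group size of 11 is borrowed from staff.
- Training groups in Phase 2 may be formed from a day's admissions. Group and site-day would then coincide in the trained arm, and two separate terms could not be estimated there.
- The planned baseline adjustment could offset the power loss, as the sensitivity check shows.

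These objections narrow the claim but do not remove it. The article itself publishes a sample size, and that figure equals the independent-observations result beside a stated group delivery. The offset from baseline adjustment rests on a correlation that the stated power calculation does not use, and clustering still reduces whatever power the adjustment yields.

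**Conclusion.** The point holds in a conditional form. Group delivery is stated, clinic is the only grouping factor named, and the Phase 2 sample size contains no allowance for clustering. If responses to training differ between sessions and no group term is fitted, standard errors are understated for the Phase 1 change and for the Phase 2 arm comparison.

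Under the assumed ICCs of 0.02 to 0.10 and groups of 11, unadjusted Phase 2 power falls from 80% to between about 77% and 63%. Ignoring the clustering raises Phase 2 type I error to between about 6% and 11%. ICC and Phase 2 group size are both assumptions. This should be changed, with medium confidence; it does not invalidate the design.

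**What to change.** - Record a training-group ID for every trained participant.
- **Phase 1:** add a random effect for training session, with small-sample degrees of freedom (Kenward-Roger or Satterthwaite), because there are only about 12 to 14 sessions.
- **Phase 2:** fit a partially nested model with a training-group term in the trained arm only. State how groups are formed; where they follow admission day, combine this term with the site-day term instead of fitting both.
- **Phase 3:** use the same term only where trained participants were in fact trained in groups.
- Restate Phase 2 power over a range of ICC and group size, and state the baseline-adjustment assumption explicitly.

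The cost is one extra variable and some analysis wording. No extra participants are required, but the stated power becomes somewhat less favourable.

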#### Statistical analyses

Training effects will be tested by evaluating differences between the measurement times using linear and general mixed models. Baseline values of the first measurement time point will be considered as covariates. Clinics are modeled as fixed effect. Key demographic variables such as age, gender and occupation will be used to calculate selectivity in dropout rates. Missing data per measurement point, but also over time, will be treated by advanced methods to handle missing data such as the full information maximum likelihood method (FIML; this will be the same in all other phases, too).

### Phase 2: quasi-experimental efficacy study

#### Aim/overview of research questions and methods

In Phase 2 (see Fig. 2 and Fig. 5 in Appendix), the effectiveness of the communication competences intervention for the target group of patients and their social support providers will be tested using the gold standard, i.e. a randomized control trial (RCT). This intervention will be based on all stages of Phase 1 of this project, and thus will be developed in a participatory approach with patients and professionals working in the clinics [63]. The intervention will enable patients and social support providers to gain knowledge about the prevalence of pAEs and communication problems as well as expectations of action results. Moreover, it will allow participants to practice communication competences and develop their self-efficacy. Furthermore, the intervention will utilize the provided theoretical input in order to integrate theory into everyday hospital life by means of action and coping plans. To implement the acquired competences as effectively as possible, the following three components will be addressed in the intervention [65]:
the motivation or intention to communicate effectively and confidently with each other,the knowledge of what is crucial for effective communication,the ability to communicate effectively.

The intervention is based on the HAPA model as a social-cognitive model for behavioral change [25] and communication competences (see description of the training above in Phase 1). Participants will be trained in groups by specialized instructors over the course of one and a half days in facilities of the participating clinics (see Table 5, and  Fig. 5 in Appendix).

#### Procedure

In each hospital, four *professionals will be taught in a train-the-trainer seminar* to train patients and their social support providers based on the short manual developed to teach communication competences. Recruitment will take place via the doctors, nurses and midwives in the hospitals (Fig. 5 in Appendix). The quality management departments will be involved to ensure adequate enrollment in order to reach the target sample size of N = 423 participants. Informed consent will be collected by on-site project managers. When an expectant mother is admitted to the clinic and agrees to participate in the study, she will be randomly assigned to a training group (IG) or a control group (CG). If she is accompanied by a partner, relative, or close friend, they will be assigned to the same group. All patients and social support providers randomly assigned to the intervention group will receive the same training content over the course of this study. In contrast, the control group will receive the hospital care-as-usual (see Fig. 5 in Appendix).

*Randomization* will be done per site and day (block randomization). The central project coordinator will generate the allocation sequence. Depending on this sequence, all patients admitted to the hospital on that day will be allocated to either the IG or to the CG. Patients and staff will not be informed beforehand on which days allocation to the IG or the CG takes place to prevent biases. Instead, the on-site project manager at each hospital will receive a sealed envelope each day containing this information, enabling them to inform other staff involved as well as enroll and assign participants to the CG or IG treatment. This process allows trial participants, general care providers, outcome assessors and data analysts to remain blinded throughout the allocation sequence. Trial participants and general care providers will be unblinded in case they ask for more information about the training. Revealing a participant’s allocated intervention during the trial can be performed after completion of the IG treatment to disclose the content of the intervention. A flyer will be provided containing this information, which will be also used after the study to disseminate findings and tools. Inclusion and exclusion criteria are outlined in Table 6.

**Table 6 Tab6:** Summary of the inclusion and exclusion criteria

*Inclusion criteria*	*Exclusion criteria*
Expectant mother or *patient* in gynecology and obstetrics or *social support providers* (spouse/partner, relative, close friend) to be recipient of the training *Professional* in a gynecology and obstetrics hospital to be trainer of the patients and the social support providers	Not proficient in the German language and/or does not have the capability of writing Severe cognitive deficits (unable to read/write/answer questions) and impairments due to diagnosed brain injuries, neurological disorders, etc. Insufficient corrected eyesight (patients must be able to read on the cell phone) Participation in another research study or intervention trial conducted in the clinic
Aged 18 years and above	Younger than 18 years
Healthy volunteers	High risk, emergency case
Declaration of consent for participation in the study	Withdraw of consent for participation in the study at any point in time

According to a power analysis, a sample of *N* = 352 is necessary (alpha error = 0.05, power = 80%, to be analyzed IG _analysis_: *N* = 176; CG _analysis_: *N* = 176) in order to detect an effect size of *d* = 0.3. With an assumed drop-out rate of 20%, *N* = 423 participants (IG _recruited_: *N* = 212; CG _recruited_: *N* = 211) have to be recruited in the study. The pAEs will be collected on an individual basis (anonymized) and coded according to the communication competences (see Fig. 5 in Appendix).

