**Methods:**

The study will take place in two maternity clinics in Germany. In line with previous studies of complex interventions, it is divided into three interdependent phases. Each phase provides its own methods and data. Phase 1: Needs assessment and a training for staff (*n* = 140) tested in a pre-experimental study with a pre/post-design. Phase 2: Assessment of communication training for patients and their social support providers (*n* = 423) in a randomized controlled study. Phase 3: Assessment of an app supporting the communication between staff, patients, and their social support providers (*n* = 423) in a case-control study. The primary outcome is improvement of communication competencies. A range of other implementation outcomes will also be assessed (i.e. pAEs, patient/treatment satisfaction, work satisfaction, safety culture, training-related outcomes).

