#### Statistical analyses

To test the effectiveness of the digital app, a case-control study will be performed (see Fig. 6 in Appendix). Cases are newly recruited individuals that fulfil the inclusion criteria outlined in Table 6. Comparators/controls are the participants in one of the two intervention arms of the previously conducted RCT study in Phase 2 (i.e. patients; historical control groups; No-Treatment CG _analysis_: *N* = 176; No-Treatment CG _recruited_: *N* = 212; Previously Treated/Active CG _analysis_: *N* = 176 (called IG1 in Fig. 6 in Appendix); Previously Treated/Active CG _recruited_: *N* = 212, see in section Phase 2). *N* = 176 participants need to be analyzed for the intervention group (IG2 _analysis_). Assuming a drop-out of 20%, *N* = 212 participants have to be recruited for the intervention group (IG2 _recruited_) in Phase 3 (see Fig. 6 in Appendix). The intervention will also be provided to the professionals in the clinic. Adoption and acceptance of the intervention will be evaluated in all groups by means of observational data and self-report. Target criteria are specified in Tables 1 and 2.

At the end of Phase 3, the results from all three phases will be disseminated using a white paper with recommendations for practice. Further plans to communicate trial results to participants, healthcare professionals, the public, and other relevant groups via publication, presentations and press releases will be developed using a participatory approach, with the restriction that anonymity is ensured at all times.

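### The Phase 2 sample size uses one N for two different units (persons of both roles, or patients only), and if it counts both roles the stated 80% power is not delivered by the stated calculation

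*Protocol article*

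**What the plan says.** All references are to the protocol article.

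- **Abstract, Methods.** Phase 2 is described as "Assessment of communication training for patients and their social support providers (*n* = 423) in a randomized controlled study". The figure 423 follows a phrase that names both roles.
- **Phase 2, Procedure (allocation).** The expectant mother is allocated on admission, by site and day. For her companion: "If she is accompanied by a partner, relative, or close friend, they will be assigned to the same group".
- **Phase 2, Procedure (Table 6 and sample size).** Table 6 lists support providers beside patients as eligible recipients of the training. The power statement says "a sample of *N* = 352 is necessary (alpha error = 0.05, power = 80" per cent) for an "effect size of *d* = 0.3", split as "IG _analysis_: *N* = 176; CG _analysis_: *N* = 176". It then allows for 20% drop-out to reach 423, called simply participants. It gives no number of women or dyads and no within-dyad correlation.
- **Phase 2, Statistical analyses.** Because mothers and support providers both take part, dyadic data are to be analysed.
- **Phase 3, Statistical analyses.** The two Phase 2 arms return as controls, with the same 176 analysed per arm, and are glossed as "i.e. patients; historical control groups; No-Treatment CG".

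**The concern.** A woman and her companion always share an arm, so they are not two independently allocated units, and their answers are likely to be correlated. A calculation that treats every person as independent overstates the information in a pooled analysis of both roles. For outcomes that arise only on the woman's side, the number that counts is the number of women, which falls below 352 as soon as companions are included in that total.

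The clearest such outcome is preventable adverse events (pAEs). Table 2 lists them under primary outcomes, and the Background describes them as injury to the pregnant woman, fetus or newborn.

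There is also a practical consequence. Staff recruiting to 423 cannot tell from the article whether a couple counts as one or two. If Phase 2 stops at 423 persons, the arms passed to Phase 3 will contain fewer patients than Phase 3 says it has.

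**Working it through.** **Inputs from the article (Phase 2, Procedure):** alpha 0.05, power 80%, d = 0.3, 176 + 176 = 352 analysed. Sidedness is not stated; two-sided reproduces the figure.

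**Assumed, not in the article:** f, the share of women accompanied by one enrolled companion; rho, the within-dyad correlation of the outcome; r, the correlation between baseline and follow-up scores.

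**1. Reproducing the plan's figure.** The exact two-sided two-sample t-test for d = 0.3 needs 175.4, hence 176 per arm, with power 0.801. So 352 is the independent-observations number and contains no allowance for dyads. (423 is 352 × 1.2 = 422.4, rounded up. The figures below take 352 analysed as given.)

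**2. If the 352 are persons of both roles, pooled analysis.** The share of persons who belong to a dyad is 2f/(1 + f). The design effect is 1 + rho × 2f/(1 + f), and the effective number per arm is 176 divided by it.

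| f | rho | Design effect | Effective n per arm | Power at d = 0.3 |
|---|---|---|---|---|
| 50% | 0.1 | 1 + 0.1 × 0.667 = 1.067 | 165.0 | 0.78 |
| 50% | 0.3 | 1.20 | 146.7 | 0.73 |
| 50% | 0.5 | 1.33 | 132.0 | 0.68 |
| 100% | 0.1 | 1.10 | 160.0 | 0.76 |
| 100% | 0.3 | 1.30 | 135.4 | 0.69 |
| 100% | 0.5 | 1.50 | 117.3 | 0.63 |

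Because both members share an arm, any positive rho takes unadjusted power below 80%.

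**3. If the 352 are persons of both roles, women only.** Women per arm = 176/(1 + f).

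| f | Women per arm | Power at d = 0.3 | d detectable with 80% power |
|---|---|---|---|
| 25% | 140.8 | 0.71 | 0.34 |
| 50% | 117.3 | 0.63 | 0.37 |
| 100% | 88.0 | 0.51 | 0.42 |

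For pAEs, which are judged by number and severity, d = 0.3 is only a stand-in. The table shows the loss of numbers, not the true power for that outcome.

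**4. If the 352 are women.** Women per arm stay at 176 and women-only power at 0.80. Companions are then additional, and the abstract's 423 is not the combined number it appears to be.

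**5. What baseline adjustment could recover.** With a baseline covariate, the effective n becomes n/(1 − r²).

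- Pooled, design effects 1.2 / 1.3 / 1.4: power 0.77 / 0.73 / 0.70 at r = 0.3, and 0.84 / 0.81 / 0.78 at r = 0.5.
- 88 women per arm: 0.63 at r = 0.5 and 0.79 at r = 0.7.

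None of these figures includes the effect of allocating by site and day.

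**The case against.** The strongest reply is that the article nowhere says outright that a couple counts as two. Phase 3 calls the same arms patients, and on that reading women-only power is as stated. The abstract is weak evidence of a head count: it also attaches 423 to staff, patients and support providers for Phase 3, while the Phase 3 section builds its groups from arms of patients. This stands. A reader might infer that the trial's power is simply 50% to 65%. The documents do not support that: it requires the both-roles reading and about 43% or more of women accompanied, and no such share is given.

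Second, the Phase 1 analysis uses baseline values as covariates, and Phase 2 is to be analysed in the same way, so some or all of the lost power may return. This also stands. A reader should not conclude that 80% is unattainable, only that the published calculation does not show it.

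Third, satisfaction might be taken as a woman-only outcome. Table 2 lists patient and treatment satisfaction for patients and support providers, so it is not. Communication competence is likewise hypothesised for both roles.

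Fourth, dyad numbers and correlations may be in the fuller German protocol, and dyadic analysis is already planned. That excuses missing detail. It does not remove the conflict between the abstract and Phase 3 over what the published N counts, and a dyadic model does not change the number on which the power statement rests.

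**Conclusion.** The point holds as an inconsistency in the unit of N, with a conditional consequence for power. The arithmetic of 352 is correct for independent observations, but the article uses that N for both roles in one place and for patients in another. The same calculation cannot support 80% on both readings.

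- **Persons of both roles:** unadjusted pooled power is about 63% to 78% (rho 0.1 to 0.5, f 50% to 100%). Women-only power is about 71% / 63% / 51% at f = 25% / 50% / 100%. The Phase 2 arms fall short of 176 patients whenever companions are counted.
- **Women only:** women-only power stays at 80% before any site-day clustering, and the abstract's figure is mislabelled.

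The values of f, rho and r are assumptions. The article does not settle which reading applies, so no single power figure can be put in place of 80%.

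**What to change.** State whether 423 and 352 count women (dyads) or persons. Bring the abstract, the Phase 2 allocation and sample-size text, and the Phase 3 control-group description into line, with the same unit throughout.

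Keep the planned enrolment and restate power, or the detectable d, in two parts:

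1. For the pooled dyadic analysis, with a stated within-dyad correlation and accompanied share, and any gain assumed from baseline adjustment.
2. For women-side outcomes, with the expected number of women.

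Note beside these that allocation by site and day is a further level of clustering not covered by either figure. Which role's score is primary need not change.

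The cost is a text revision and, if N counts persons, less favourable stated power.
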